### Randomization, allocation concealment and blinding

Once the groin incision is primary closed, randomization will be done using internet-based software, sealedenvelope.com (London, UK), via random permutated blocks. If the patient has bilateral groin incisions, the right groin will be randomized and the left groin will be automatically placed in the other arm. The surgical team, clinical staff, and patient will not be blinded to the intervention status. The primary outcome of SSI will be assessed by a clinical specialist nurse who will be blinded to the intervention status.

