### Definition of primary endpoint and outcome measures

The primary endpoint is the incidence of superficial SSI within 30 days of surgery. SSI is defined by the Center for Disease Control and Prevention (CDC) criteria [15] as: infection occurring within the first 30 postoperative days involving skin and subcutaneous tissue of the incision and at least one of the following:Purulent drainage from the incisionOrganisms isolated from an aseptically obtained culture of fluid or tissue from the incisionAt least one of the following signs/symptoms of infectionPain or tendernessLocalized swellingRednessHeatOR incision is deliberately opened by a surgeon (unless incision is culture negative)4.Diagnosis of SSI by the surgeon or attending physician

Once the SSI is identified, the Szilagyi classification of vascular wound infections will be used to classify to infection [16]. This classification categorizes vascular SSI based on dermal involvement (I), subcutaneous involvement (II) or arterial graft involvement (III).

SSI will be assessed daily, at discharge, and reassessed at the outpatient clinic within 30 days following the operation.

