### Sample size

Our previous study revealed a SSI rate of 22 % in all patients requiring femoral artery exposure for vascular surgical procedure at LHSC [4]. This study will only include high-risk patients as defined above and we expect the wound infection rate to be higher. Matatov et al. demonstrated a reduction of groin SSI with NPWT from 30 % to 6 %, an absolute risk reduction of 24 % and relative risk reduction of 80 % [6]. Given an alpha of 0.05, for 80 % power, this yields a required sample size of 48 patients per group using the Fleiss method with continuity correction. The planned sample size will account for potential loss of follow-up, device malfunction and patient incompliance and has been adjusted to a final sample size of 54 (10 % increase from calculated sample size) groin incisions per group and a total study sample of 108 groin incisions. The timeline for recruitment is 20 months and with a 90-day follow-up the study will be concluded in 2 years.

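### Criterion 3 of the primary SSI definition joins signs and deliberate opening of the wound by OR, so one non-specific sign meets it and the culture-negative exception does almost nothing

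*Protocol article*

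**What the plan says.** The section on the primary endpoint states: "The primary endpoint is the incidence of superficial SSI within 30 days of surgery". It attributes the definition to the CDC criteria (reference 15). The definition asks for an infection within 30 days "involving skin and subcutaneous tissue of the incision and at least one of the following", and four criteria follow.

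The first two are purulent drainage and an organism grown from an aseptically obtained culture. The third needs at least one sign or symptom of infection, and its list runs on into the alternative of opening: "or tendernessLocalized swellingRednessHeatOR incision is deliberately opened by a surgeon (unless incision is culture" negative). The fourth is numbered separately: "4.Diagnosis of SSI by the surgeon or attending physician". The list items were run together when the PDF was read, but the capitalised OR and the numeral 4 are intact, so the structure is clear.

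On who knows the allocation, the randomization and blinding section says: "The surgical team, clinical staff, and patient will not be blinded to the intervention status". Its next sentence says: "The primary outcome of SSI will be assessed by a clinical specialist nurse who will be blinded to the intervention status".

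The Sample size section takes its rates from a retrospective study that "demonstrated a reduction of groin SSI with NPWT from 30 % to 6" per cent. It continues: "Given an alpha of 0.05, for 80 % power, this yields a required sample size of 48 patients per group", by the Fleiss method with continuity correction, raised to 54 groin incisions per group.

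**The concern.** Any one of the four criteria is enough, and within criterion 3 any one sign is enough. Tenderness and some swelling or redness are plausible at a fresh groin incision without infection. A literal reader could therefore record a primary event with no pus, no organism, no opening and no clinician's diagnosis.

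The text itself suggests that OR is not what was meant. The exception for a negative culture exists to remove opened wounds that prove uninfected. Under OR it removes only a wound that was opened, was culture-negative and had no pain, tenderness, swelling, redness or heat. Any other opened, culture-negative wound returns through the list of signs. The exception does real work only if opening and signs are required together.

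False-positive events at the same rate in both arms shrink the relative and absolute effect, add variance and cost power. They also make it uncertain that the planning rates describe the endpoint being counted.

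**Working it through.** **Inputs.** From the Sample size section: 30% (standard dressing) and 6% (NPWT), alpha 0.05, 80% power, 48 per group before inflation and 54 after. From the Statistical analysis section: two-sided tests. Assumed, because the documents give no value: f, the share of uninfected groins counted as SSI on a sign alone, equal in both arms. All 54 per group are taken as analysed.

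**Step 1. Reproduce the plan's figure.** With d = p1 − p2 and p̄ = (p1 + p2)/2, the uncorrected size is

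n0 = [1.96·√(2p̄(1−p̄)) + 0.842·√(p1(1−p1) + p2(1−p2))]² / d².

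For 0.30 and 0.06 this is 39.03. The continuity-corrected size is n = (n0/4)·[1 + √(1 + 4/(n0·d))]². It gives 46.99, so 47; if n0 is first rounded up to 40, it gives 47.97, so 48. The plan's 48 is reproduced. Inflation: 48/0.90 = 53.3, so 54, as stated.

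**Step 2. Add sign-only events.** The observed rate becomes p′ = p + f(1 − p). For f = 10%: control 0.30 + 0.10 × 0.70 = 0.370; NPWT 0.06 + 0.10 × 0.94 = 0.154.

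**Step 3. Power at n per group, with continuity correction.**

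Power = Φ{ [d − 1/n − 1.96·√(2p̄(1−p̄)/n)] / √[(p1(1−p1) + p2(1−p2))/n] }.

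At n = 54 and f = 0: (0.240 − 0.0185 − 1.96 × 0.0739)/0.0702 = 1.09, so 86.2%.

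| f (assumed) | Control v NPWT | Absolute reduction | Relative reduction | Power at 48 | Power at 54 | n per group for 80% |
|---|---|---|---|---|---|---|
| 0 | 30.0% v 6.0% | 24.0 points | 80% | 81.0% | 86.2% | 47 |
| 5% | 33.5% v 10.7% | 22.8 points | 68% | 69.3% | 75.5% | 60 |
| 10% | 37.0% v 15.4% | 21.6 points | 58% | 58.8% | 65.0% | 73 |
| 20% | 44.0% v 24.8% | 19.2 points | 44% | 42.1% | 47.5% | 106 |

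Even at 5%, power at the full 54 per group is below the planned 80%.

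**Step 4. Look for a passage that narrows the rule.** The secondary endpoints, data collection and analysis sections add no further condition. The Szilagyi grade is assigned only after an SSI has been identified, so it screens nothing out.

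**The case against.** The strongest reply is that the definition is conjunctive. It requires an infection of skin and subcutaneous tissue as well as a criterion, and criterion 3 speaks of signs of infection. Ordinary incisional soreness, judged not infective, would fail both. This stands in part: a sensible assessor will not count every tender groin. But the article offers no test of infection other than the four criteria, so the lead-in relies on unstated judgement.

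A reader might infer that the OR lets knowledge of treatment drive the endpoint. The documents do not support that in general. A blinded nurse assesses the outcome, and swelling, redness and heat are examined signs. What remains is narrower: pain is reported by patients who know their dressing.

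A reader might also infer that the definition contradicts the 30% and 6% rates. The article does not say how the retrospective study defined SSI, so a mismatch is possible but not shown.

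Finally, requiring opening as well as a sign makes criterion 3 depend on a decision by an unblinded surgeon, and criterion 4 is already a clinician's diagnosis. That is a real cost of the correction and has to be managed. It does not justify leaving the present wording.

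**Conclusion.** Criterion 3 is wrong as written. The OR makes one non-specific sign sufficient and leaves the culture-negative exception almost without effect. That conclusion rests on the text alone and does not depend on the cited CDC source, which was not available for comparison.

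The numerical consequence is conditional. For assumed false-positive shares of 5% to 20%, equal in both arms, the relative reduction falls from 80% to between 68% and 44%, and power at 54 per group from 86.2% to between 75.5% and 47.5%. The true share is unknown and could be lower if assessors apply judgement. The planning rates may therefore not apply to this endpoint; it cannot be said that they do not.

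It is tempting to go further and say that sign-only events would favour one arm because the two dressings expose the wound at different times. The documents give nothing from which to establish or size such a difference, and the calculation does not assume one.

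**What to change.** - Reconcile criterion 3 with the cited CDC definition (reference 15), so that a sign or symptom counts only together with deliberate opening of the incision, unless culture-negative. In the text this changes OR to AND.
- Record which criterion each SSI met.
- Have the nurse who is blinded to arm re-classify any event already recorded on a sign alone. The article reports 46 patients enrolled, so this should be done, and documented, before any comparison by arm.
- Report SSIs by criterion met as a sensitivity analysis, because criterion 3 will then depend on an unblinded surgeon's decision to open.

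**Cost.** An amendment to the endpoint wording, one extra field on the paper form, and a blinded re-check of events so far. The planned 48 and 54 per group do not change. The observed event rate will be lower than under the present wording. In the scenarios above, control falls by 3.5, 7.0 or 14.0 points (33.5 − 30, 37 − 30, 44 − 30) and NPWT by 4.7, 9.4 or 18.8 points (10.7 − 6, 15.4 − 6, 24.8 − 6). Infections without pus, a positive culture or opening would then enter only through the clinician's diagnosis in criterion 4.

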### Secondary endpoints

Secondary endpoints include length of stay, emergency room visits, SSI requiring surgical intervention, deep SSI occurring within 90 days of an operation, limb amputation, and mortality. A cost analysis will also be performed using the average cost provided by LHSC for inpatients, return visits, and any surgical intervention. Outcomes related to potential harm will also be identified including local reaction to the NPWT device, and the need for early removal of the dressing.

### Sample size

Our previous study revealed a SSI rate of 22 % in all patients requiring femoral artery exposure for vascular surgical procedure at LHSC [4]. This study will only include high-risk patients as defined above and we expect the wound infection rate to be higher. Matatov et al. demonstrated a reduction of groin SSI with NPWT from 30 % to 6 %, an absolute risk reduction of 24 % and relative risk reduction of 80 % [6]. Given an alpha of 0.05, for 80 % power, this yields a required sample size of 48 patients per group using the Fleiss method with continuity correction. The planned sample size will account for potential loss of follow-up, device malfunction and patient incompliance and has been adjusted to a final sample size of 54 (10 % increase from calculated sample size) groin incisions per group and a total study sample of 108 groin incisions. The timeline for recruitment is 20 months and with a 90-day follow-up the study will be concluded in 2 years.

### Data collection and management

All data collected will be recorded on paper forms and will be kept within the patient charts. Data will be collected by the surgical team and trial personnel. Accuracy of data collection will be ensured by the study personnel not involved with data management or analysis by performing sample assessments at regular intervals. Any adverse events due to NPWT that causes morbidity or mortality will be recorded and reported to the primary investigator and institutional ethics committee. We expect minimal to no harm from the use of NPWT in this trial based on a previous report using the same device [6].

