**Methods/design:**

In this single-center, prospective randomized controlled trial, patients scheduled for a lower limb revascularization requiring open femoral artery exposure who are at a high risk (BMI > 30 kg/m^2^, previous femoral cutdown or Rutherford V or VI category for chronic limb ischemia) will be eligible for the study. A total of 108 groin incisions will be randomized to the use of a negative pressure wound device or standard adhesive gauze dressing. Patients will be followed in hospital and reassessed within the first 30 days postoperatively. The primary outcome is SSI within the first 30 days of surgery and will be determined using the intention-to-treat principle. Secondary outcomes include length of stay, emergency room visits, reoperation, amputation and mortality. A cost analysis will be performed.

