### Intervention and control

The intervention group will have NPWT, the Prevena Incision Management System (Kinetic Concepts Inc, San Antonio, TX, USA), applied to the primary closed groin incision. The Prevena system has a silver interface with a foam layer connected to a small portable battery-operated vacuum unit. The vacuum is preset to continuous at 125 mmHg. The device is applied under sterile conditions in the operating room and remains on the patient until the hospital discharge or postoperative day 8, whichever occurs first. The wound will be inspected for any evidence of infection once the Prevena is removed. The device is used only once and is disposed of at the end of the study. Any concern about the wound or the device will require removal of the NPWT earlier than planned and will be recorded as a secondary endpoint of the trial.

The control group will have a standard sterile gauge dressing to cover the groin incision. The postoperative management is typically removal of the dressing on day 2 postoperatively with daily dressing changes thereafter. All other pre- and postoperative care of patients will be the same in both groups. Hair will be removed with electric clippers preoperatively. Skin preparation will be done with 2 % chlorhexidiene. Every patient will received preoperative antibiotics (cephalexin or vancomycin if penicillin allergy is present) and postoperative antibiotics will be given for 48 h. At the end of the operation, the groin incision will be primary closed with either skin staples, monocryl or prolene sutures.

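### Local skin and non-SSI wound events are recorded by attribution to NPWT, so they have no stated control-arm counterpart and cannot be compared between arms

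*Protocol article*

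**What the plan says.** Four parts of the protocol article bear on the recording of harm.

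- **Data collection and management** gives the adverse-event rule: "Any adverse events due to NPWT that causes morbidity or mortality will be recorded and reported to the primary investigator and institutional ethics committee". No parallel rule is given for the gauze dressing, or for events irrespective of cause.
- **Secondary endpoints** adds: "Outcomes related to potential harm will also be identified including local reaction to the NPWT device, and the need for early removal of the dressing".
- **Intervention and control** ties the second of those items to the device: "Any concern about the wound or the device will require removal of the NPWT earlier than planned and will be recorded as a secondary endpoint". For the control arm it says: "The postoperative management is typically removal of the dressing on day 2 postoperatively with daily dressing changes thereafter".
- **Randomization, allocation concealment and blinding** states: "The surgical team, clinical staff, and patient will not be blinded to the intervention status". The blinded nurse's role is described for the SSI outcome only.

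Other outcomes are not tied to the device. The Secondary endpoints section begins "Secondary endpoints include length of stay, emergency room visits, SSI requiring surgical intervention, deep SSI occurring within 90 days of an operation, limb amputation, and"; death is the final item in that list. The Abstract also lists reoperation. The Statistical analysis section compares secondary outcomes between the groups.

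**The concern.** A harm can be compared between arms only if it is looked for and recorded in the same way in both. A rule that admits an event because it is attributed to one of the two treatments cannot do this, since no event under the gauze dressing can qualify.

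The events in question are not peculiar to the device. The Abstract describes the control as a "standard adhesive gauze dressing", and the exclusion of patients with known adhesive sensitivity shows that the authors regard adhesive reaction as a risk. Haematoma, fluid leak and wound separation can follow any closed groin incision. The Discussion credits NPWT with removing fluid and reducing oedema, so the device might even lower the rate of some of them. One-arm recording could therefore hide a benefit as easily as a harm.

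At stake is the local part of the benefit-harm balance, for a preventive device whose results are meant to inform perioperative practice.

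**Working it through.** No arithmetic applies. The article gives no rate for local events, and its sample size (48 per group, raised to 54) rests on SSI rates of 30% and 6% alone. The check is to take each kind of harm and ask whether the text gives it a definition that a groin in either arm can meet.

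| Harm | Where stated | Can a control groin or patient count? | Depends on attribution? |
|---|---|---|---|
| Mortality, amputation | Secondary endpoints | Yes | No |
| SSI needing surgery, deep SSI to 90 days | Secondary endpoints | Yes | No |
| Reoperation | Abstract, Methods/design | Yes | No |
| Emergency visits, length of stay | Secondary endpoints | Yes | No |
| Local reaction | Secondary endpoints | No: worded as a reaction to the NPWT device | Yes, by its wording |
| Early removal | Secondary endpoints; Intervention and control | Not in a comparable sense | No |
| Any other adverse event | Data collection and management | No: must be attributed to NPWT and cause morbidity or mortality | Yes |

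**Early removal.** The Secondary endpoints section speaks of the dressing in general, but the operative definition under Intervention and control is removal of NPWT ahead of plan. NPWT stays on until discharge or postoperative day 8, whichever is first, while gauze typically comes off on day 2. Early removal therefore has no matching meaning in the control arm.

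**What remains uncovered.** An event falls outside the two-arm endpoints if it is local, is not an SSI, and leads to no reoperation, emergency visit or longer stay. Examples are a skin reaction, blistering, a small haematoma, a fluid leak or a minor wound separation. Under NPWT such an event has a stated route into the data, if it is called a device reaction, prompts early removal, or is attributed to NPWT and causes morbidity. Under gauze it has none.

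**Who decides.** The article does not say who judges that an event was caused by NPWT. The surgical team, which is unblinded, collects data together with trial personnel. That unblinded staff make the judgement is an inference; what the text does show is that no blinded assessor is named for it.

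**Whether the data could be collected.** The primary endpoint section has SSI assessed daily, at discharge and in clinic within 30 days. Wounds in both arms are therefore already examined at the times needed.

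**The case against.** A reader might infer that the trial has harms data for one arm only, or that its harms cannot be compared at all. The documents do not support that. The most serious outcomes are endpoints in both arms, carry no causal condition and are compared. A control-arm haematoma that led to reoperation, an emergency visit or a longer stay would be counted. The SSI criteria also include pain, swelling, redness and heat, so some local signs will be noticed in both arms. This limits the point to lesser local events and rules out any claim that control-arm wound problems have no way into the data.

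The rule can also be read as an escalation requirement for device-related events, which does not forbid recording others. The list of harm outcomes is open-ended, and early removal needs no attribution. All this is fair, but none of it supplies a control-arm definition for a local reaction or a non-SSI wound event.

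The article condenses a fuller protocol, so missing forms or definitions would be no finding. Here, however, the text does state a rule, and that rule makes attribution the condition for recording. The point concerns what is fixed, not what is left out.

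Finally, two-arm recording would still be done by people who know the allocation. That stands as a limit of the remedy.

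**Conclusion.** The point holds in a limited form. For local skin reactions and non-SSI wound events outside the listed secondary endpoints, the plan as written yields device-attributed events in the NPWT arm with nothing defined to set against them. No between-arm comparison of these events is possible.

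The size cannot be quantified. The article gives no background rate for such events and no basis for guessing how often they would be attributed to the device, so a numerical illustration would only return its own assumptions. The SSI analysis, the 54 groins per group and the comparison of serious outcomes are unaffected.

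The conclusion assumes that the stated rule is the operative one and that no fuller document already requires cause-neutral recording in both arms. It does not depend on who makes the attribution. It is worth acting on as a cheap improvement, not as a threat to the main result.

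**What to change.** Amend the Secondary endpoints and Data collection and management sections as follows.

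1. Record local skin and wound events (for example skin reaction, blistering, haematoma, fluid leak, wound separation) for every groin in both arms. Use the same definitions and the assessment times already set for SSI, whatever the suspected cause.
2. Enter attribution to the device in a separate field, so that it describes an event and does not decide whether the event is recorded. Reporting of device-related events to the ethics committee can continue alongside.
3. Compare the proportion of groins with each event between arms.
4. In bilateral patients, who have one groin in each arm, local events can be compared by groin. Patient-level events cannot be assigned to one arm and should be reported separately.

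The cost is a form change and a small amendment, with slightly more data entry for control groins and no change to visits or sample size. Recording would remain unblinded, and the trial is sized for SSI, so the comparison should be presented as an estimate with its interval rather than as a decisive safety test.
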